## Abstract

**Background:**

HPV vaccination reduces the risk of cervical cancer. Uptake however, of the ‘catch-up’ campaign in England for 17-18 year old girls is below the 80% NHS target**.** The aim of this randomized controlled trial is to assess the impact of financial incentives on (a) the uptake and completion of an HPV vaccination programme and (b) the quality of the decisions to undertake the vaccination.

**Method/Design:**

One thousand (n = 1000) 16-18 year-old girls will be invited to participate in an HPV vaccination programme: Five-hundred (n = 500) will have received a previous invitation to get vaccinated but will have failed to do so (previous non-attenders) and 500 will not have previously received an invitation (first-time invitees). Girls will be randomly selected from eligible participants who are registered with a GP in areas covered by the Birmingham East and North (BEN) and Heart of Birmingham Primary Care Trusts. The two samples of girls will be randomised to receive either a standard vaccination invitation letter or an invitation letter including the offer of vouchers worth £45 for receiving three vaccinations. Girls will also complete a questionnaire to assess the quality of their decisions to be vaccinated. The primary outcome will be uptake of the 1^st^ and 3^rd^ vaccinations. The secondary outcome will be the quality of the decisions to undertake the vaccination, measured by assessing attitudes towards and knowledge of the HPV vaccination.

**Discussion:**

The key results will be: a) the effectiveness of financial incentives in increasing uptake of the 1^st^ and 3^rd^ vaccinations**;** b) the role of participants’ socio-economic status in the moderation of the impact of incentives on uptake; and c) the impact of incentives on the quality of decisions to undertake the HPV vaccinations.

## Background

Human Papillomavirus (HPV) is an ubiquitous sexually transmitted virus that could lead to cervical cancer [1,2]. HPV vaccines help prevent infection by some of the most common forms of HPV that are associated with later development of cancer [3,4]. The HPV immunisation process takes six elapsed months and is conducted in three stages: 1^st^ vaccine, 2^nd^ vaccine two months later, and a 3^rd^ vaccine six months after the first vaccination. Completion of all three vaccinations is necessary to effectively reduce the risk of cervical cancer [5]. The degree of protection afforded by incomplete immunisation is currently unknown [6].

Since September 2008 a national programme has started in England and Wales aiming to vaccinate girls aged 12-13 against HPV. A two-year ‘catch-up’ campaign that offers the HPV vaccine to 17-18 year old girls has also been initiated. The objective of these HPV vaccination programmes is to provide three doses of the HPV vaccine to females before they become sexually active, when the risk of HPV infection and subsequent cervical cancer development increases. It is estimated that if this objective is met and vaccination coverage is sufficiently high (80% of the target population), up to 400 deaths per year in England could be prevented [7]. Although the national programme in England aimed at 12-13 year-old girls has resulted in high uptake (88.1% uptake of the first vaccination and 80.1% of the third vaccination), the uptake rates for the “catch-up” campaign in England (targeting 17-18 year olds) have been lower, with 62.2% of the target group receiving the first dose and 31.8% the third [7].

Offering girls financial incentives to undergo the HPV vaccination could increase these uptake rates. Incentive mechanisms are increasingly being considered and used in health care policy in the UK and elsewhere in an attempt to change health-related behaviour [8,9]. They are most effective in changing ‘simple’, ‘one-off behaviours’ such as getting vaccinated [10-12]. Their effectiveness however, has been predicted to vary with recipients’ level of social deprivation. Specifically, it has been argued that the most socially deprived should respond more to financial incentives [13]. Most of the calls, to use incentives in HPV vaccination programmes in the UK have so far focused on incentivising those providing the vaccination (e.g. GPs) rather than vaccination recipients [14]. Their effectiveness therefore in this context is currently unknown. Furthermore, no studies have assessed the role of social deprivation in the moderation of their impact on vaccination uptake.

Even if effective in improving uptake of the HPV national vaccination programme, the use of financial incentives raises concerns about the possible adverse effects they may have on the quality of people’s decisions to engage in incentivised behaviours. For example, it has been argued that the prospect of receiving a financial reward could result in the risks associated with a particular health behaviour being overlooked [15].To date, however, no known studies have assessed the mechanisms by which financial incentives influence the decision-making processes involved in engaging in an incentivised health behaviour.

In summary, further research is needed to determine the impact of financial incentives upon first, uptake of the HPV vaccination, and second, the quality of recipients’ decisions to get vaccinated. Furthermore, research is needed to determine the role of social deprivation in the moderation of the impact of financial incentives on uptake of vaccinations.

### Objectives and hypotheses

The primary objectives of the present study are:

(a) To assess the impact of financial incentives on the initial uptake (uptake of the first vaccination) and completion rates (uptake of the third vaccination) of an HPV vaccination programme.

(b) To assess the impact of financial incentives on the quality of the decision to be vaccinated as measured by attitudes towards and knowledge of the vaccination.

The secondary objective is:

(a) To assess whether the impact of financial incentives on the initial uptake and completion rates of an HPV vaccination programme is moderated by participants’ levels of social deprivation.

### Hypothesis I

Those offered financial incentives to get vaccinated against HPV are more likely to receive the first and third HPV vaccinations.

### Hypothesis II

The effect of incentives on uptake of the first and third vaccinations will be moderated by participants’ levels of social deprivation, with larger effects of the incentives being observed for the most socially deprived.

### Hypothesis III

Offering financial incentives reduces the quality of decisions to get vaccinated against HPV.

## Methods/Design

### Trial design

This is a randomised controlled trial in which two independent samples of participants are separately randomised to the offer of financial incentives for getting vaccinated.

### Participants

Participants will compromise of 16-18 year old girls, living in Birmingham. To be included in the trial, girls must fulfill the following inclusion criteria:

(a) Live in areas falling under the administration of the Birmingham East and North (BEN) and the Heart of Birmingham Primary Care Trusts

(b) Be registered with a GP within one of the two PCTs

(c) Be eligible to be vaccinated through the clinics (Sutton Cottage, Partners in Health and Dove Medical Centre)

(d) Not have been vaccinated against HPV before.

Half of the sample will consist of girls who have previously received an invitation to get vaccinated, but have failed to attend the first appointment (previous non-attenders). The remaining half will consist of girls who have not yet received an invitation to attend the vaccination programme (first-time invitees).

### Intervention

The components of the intervention used in the present HPV vaccination programme are:

### Invitation letters

All participants will receive letters inviting them to attend their first HPV vaccination session. These will be sent on behalf of the Birmingham East and North and Heart of Birmingham Primary Care Trusts, and will include the date, time and location of the allocated appointments.

### Reminder text messages

Participants attending their first vaccination appointment will be asked to inform the researchers of their mobile phone numbers. These will be used to send text messages reminding them of their subsequent vaccination appointments. These will be sent during the intervals between the first and second vaccinations and the second and third vaccinations and two days prior to the next session. An example of the wording of these messages is: *“(Name), don’t forget your HPV jab today at (time) at the (venue). Thank you”*.

### Offer of financial incentives

Participants from the two samples (i.e. previous-non attenders and first-time invitees) allocated to the incentivised groups will receive a modified version of the standard vaccination invitation letter, described above, which will include the offer of vouchers worth £45 for receiving the three vaccinations. Specifically, participants will be informed that they will receive:

£20 for the first vaccination

£5 for the second vaccination

£20 for the third vaccination

### Procedure

The trial will be run by the Birmingham East and North Primary Care Trust in collaboration with Healthy Incentives (http://www.healthyincentives.org.uk/, a social enterprise arising as a result of a partnership between the Young Foundation and the Birmingham East and North Primary Care Trust). The Birmingham East and North PCT has employed the Birmingham Primary Care Shared Services Agency (BPCSSA) to do the following: select participants to be included in the trial; randomise them to each group and post the invitation letters. Once the letters have been sent, the BPCSSA will provide the Healthy Incentives team with the details of all the participants who have been invited, including their names, addresses, scheduled vaccination dates, the participant group (previous non-attender or previously not invited) and randomisation group (incentive or not). The vaccinations for all individuals will take place at three community clinics. The BPCSSA will schedule a number of ‘incentivised only’ sessions at these clinics to avoid any tensions caused by not incentivising all groups. Vaccinations will be carried out by nurses working with Heart of Birmingham (HOB). When attending their first vaccination session and while waiting to get vaccinated, participants will be asked to sign a consent form and complete a measure assessing the quality of their decision to get vaccinated. They will also be requested to select a date for their next vaccination. Receipt of each vaccination will be contingent on completion of all the previous doses (i.e. in order to receive the 3rd vaccination participants will need to have first completed the 1st and 2nd vaccinations), with no skipping of doses being allowed. After receiving their vaccinations, participants in the incentivised groups will be provided with the appropriate shopping vouchers. Two days prior to their 2^nd^ and 3^rd^ vaccination sessions, the Healthy Incentives team will send participants text messages reminding them of their appointments.

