### Statistical analysis

To assess the impact of the intervention on initial uptake (i.e. the 1st vaccination) and completion of the HPV vaccination programme (i.e. the 3rd vaccination) logistic regressions will be performed separately for each of the two samples, i.e. for girls who have not received an invitation to get vaccinated before and those who have received a previous invitation but have failed to attend. To test the moderating effect of social deprivation on the impact of the intervention, the interaction between IMD scores and intervention will be added to the logistic regression models. To test whether there is a difference in the size of effect of the intervention in the two samples, datasets will be combined and another logistic regression conducted, in which whether participants have received an invitation to get vaccinated before or or not will be added as a predictor to the model, along with the intervention. To test for differences in the attrition rates between the 1^st^ and 3^rd^ vaccinations between the invervention and control groups the *χ*^2^ test will be used. Finally, differences in knowledge of the HPV vaccination between intervention and control group will be tested using the *χ*^2^ test, while differences in attitudes towards the HPV vaccination will be examined via a one-way analysis of variance. All tests will be assessed at the 5% level of significance.

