## Discussion

The results of the study will produce valuable information regarding the potential effectiveness of financial incentives in increasing uptake and completion of the HPV vaccinations by teenage girls. The results will also provide valuable information regarding the validity of concerns about the potentially adverse effects of financial incentives on the quality of people’s decisions to engage in incentivised behaviours. If evidence from this trial supports such concerns, further research will be needed to assess how incentives might undermine informed choice, e.g. whether they alter who attends or whether they alter the attitudes towards and/or knowledge of the target behaviour in all who are offered incentives and therefore in those who attend. The design of the present trial does not allow for such assessments to be made.

Knowledge regarding the impact of financial incentives both on uptake of the HPV vaccination and on the quality of decisions to engage in incentivised behaviours is lacking in the literature. Findings therefore, are expected to clarify these issues and have the potential to inform discussions concerning the increasing use of financial incentives for health promotion.

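### Knowledge and attitudes are measured only in girls who attend for dose 1, so the Hypothesis III tests compare attenders, not randomised groups; the objective, hypothesis and analysis should say so and account for prior invitation.

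*Protocol article*

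**What the plan says.** All places are in the protocol article.

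- **Objectives and hypotheses**, primary objective (b): "To assess the impact of financial incentives on the quality of the decision to be vaccinated". The Abstract lists decision quality as the secondary outcome.
- **Hypothesis III**: "Offering financial incentives reduces the quality of decisions to get vaccinated against HPV".
- **Hypothesis I**: "Those offered financial incentives to get vaccinated against HPV are more likely to receive the first and third HPV vaccinations".
- **Participant recruitment and randomisation**: girls are selected from a list and randomised to one of two letters, before any contact at a clinic. The two samples (first-time invitees and previous non-attenders) are randomised separately.
- **Procedure**: at the first session, "while waiting to get vaccinated, participants will be asked to sign a consent form and complete a measure" of decision quality. No section describes giving it to girls who stay away.
- **Statistical analysis**: "differences in knowledge of the HPV vaccination between intervention and control group will be tested using the" chi-square test, and "differences in attitudes towards the HPV vaccination will be examined via a one-way analysis of variance". The uptake regressions are specified separately for each sample; the sentence on knowledge and attitudes names only the two arms.
- **Discussion**: if harm is found, further research would have to establish whether incentives change who comes or change what girls know and think. "The design of the present trial does not allow for such assessments to be made".

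**The concern.** Whether a girl is measured depends on whether she attends, and attendance is what the letter is meant to alter. If the offer works, the incentive arm's respondents include girls who would not have come without it, and the control arm has no counterpart to them. A difference in mean attitude or in the proportion answering correctly can then arise purely from the changed mix, and a real change in attitudes or knowledge could equally be hidden by it.

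A second source of imbalance is the mix of the two samples. If they attend at different rates, previous non-attenders can be a different share of respondents in each arm, even though randomisation balanced the samples by design.

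At stake is one of the trial's three hypotheses. The uptake analyses are unaffected, because uptake is defined for every randomised girl.

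**Working it through.** **The plan's own figure.** The only sample-size calculation concerns dose 3 completion: 32.4% vs 40.9%, two-sided 5%, 80% power, total 1008. A pooled-variance two-proportion formula without continuity correction gives 504 per arm, 2 × 504 = 1008, so it reproduces. It has no bearing on decision quality, for which the article gives no target difference.

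**Inputs for the illustration**

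| Input | Value | Source |
|---|---|---|
| Higher base attendance at dose 1 | 62.2% | Background, national catch-up figure; its use here is an assumption |
| Lower base attendance | 10% | Assumed, for previous non-attenders |
| Gain in attendance from the offer | 8.5 points | Sample size determination, but stated there for dose 3; its use for dose 1 is an assumption |
| Adequate knowledge, girls who would attend anyway | 80% | Assumed |
| Adequate knowledge, girls drawn in by the offer | 60% | Assumed |
| Effect of the offer on any girl's own knowledge | none | Assumed, to isolate selection |

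**Step 1: selection within a sample.** With base attendance c and gain d, expected knowledge among incentive-arm attenders is (c × 0.80 + d × 0.60) / (c + d).

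- c = 0.622: (0.4976 + 0.0510) / 0.707 = 0.5486 / 0.707 = 77.6%. Apparent fall 2.4 points.
- c = 0.10: (0.0800 + 0.0510) / 0.185 = 0.1310 / 0.185 = 70.8%. Apparent fall 9.2 points.
- If the girls drawn in also have 80%, the fall is zero at any c.

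The fall equals the share drawn in, d / (c + d), times the knowledge gap. That share is 12.0% at c = 0.622 and 0.085 / 0.185 = 45.9% at c = 0.10.

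**Step 2: how often a two-sided 5% test would reject under Step 1.**

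- c = 0.622, 500 per arm (311 vs about 354 attenders): about 11%.
- c = 0.10, 250 per arm (25 vs about 46 attenders): about 12%.

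Larger assumed gaps give more. With 70% vs 30% and 500 invited per arm, rejection is about 26% at 62.2% base attendance and 47% at 20%.

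**Step 3: mix of the two samples.** The samples are equal in size, so take base attendance of 62.2% in first-time invitees and 10% in previous non-attenders, with an equal 8.5-point gain in both.

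- Control: 10 / (62.2 + 10) = 10 / 72.2 = 13.9% previous non-attenders.
- Incentive: 18.5 / (70.7 + 18.5) = 18.5 / 89.2 = 20.7%.

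The shares differ although the gain is the same in both samples. If knowledge differed by 20 points between the samples and by nothing else, an unstratified comparison would show 0.20 × (20.7 − 13.9) = about 1.4 points from the mix alone.

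**Step 4: would counting over all randomised girls solve it?** Take vaccinated without an informed decision, out of all randomised, under the Step 1 assumptions at 62.2%.

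- Control: 0.622 × 0.20 = 12.4%.
- Incentive: 12.4% + 0.085 × 0.40 = 15.8%. With 500 per arm, a 5% test rejects about 34% of the time.
- If the extra attenders are just as informed: 0.707 × 0.20 = 14.1%, still above 12.4%, and rejected about 12% of the time.

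This proportion rises with uptake itself, so it is no cleaner a test of Hypothesis III.

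**The case against.** The strongest defence is that a decision to be vaccinated exists only in girls who come to be vaccinated, so comparing attenders is the natural contrast. The Discussion treats a changed mix of attenders as one way in which incentives might undermine informed choice. On that reading, drawing in less informed girls makes Hypothesis III true rather than falsely supported. This stands as far as it goes: the contrast is a legitimate description of attenders under each policy. It does not stand for a reading that the offer altered girls' decisions, which the wording of objective (b) and Hypothesis III leaves open.

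It is also fair that the limitation is disclosed. But the disclosure appears only in the Discussion, is conditional on an adverse finding, and says nothing about selection masking an effect.

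On prior invitation, a reader might infer that the plan definitely pools the two samples. That is the plain reading of a one-way ANOVA by arm, but the text does not say it, and the detail may sit in a fuller analysis plan.

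A reader might also infer that the trial will report harm from incentives as an artefact. The document does not support that: the direction is unknown, and under the 80% vs 60% assumption a spurious significant result occurs only about 11% to 12% of the time.

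**Conclusion.** The point holds in a limited form. The knowledge and attitude tests compare girls selected after randomisation by an event the offer is meant to change. They cannot on their own support objective (b) or Hypothesis III as an effect of the offer on girls' decisions. The article acknowledges this but does not carry it into the objective, hypothesis or analysis. As worded, the tests also name no adjustment for prior invitation, although the trial randomises within those groups.

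Neither the size nor the direction of any bias can be derived from the document. The apparent falls of 2.4 and 9.2 points rest on assumed base attendance, an assumed dose 1 gain borrowed from the dose 3 effect, and an assumed 20-point knowledge gap. They shrink to zero if the extra attenders resemble the rest. The attender comparison is therefore not worthless; its conclusion needs to be limited.

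**What to change.** 1. **Statistical analysis.** Run the knowledge and attitude comparisons by sample, or adjust for prior invitation: a stratified chi-square for knowledge, and ANOVA or regression with a prior-invitation term for attitudes.
2. **Objective (b), Hypothesis III and Statistical analysis.** State that the contrast is among girls who attended for dose 1, and that a difference may reflect who attends as well as changed knowledge or attitudes.
3. **Optional.** Show vaccinated with and vaccinated without an informed decision, each out of all randomised girls, by arm and sample. This needs a cut-off set in advance and a rule for blank questionnaires. Present it as description only, not as the test of Hypothesis III, because both proportions can rise with uptake.

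The cost is wording and one extra model term or stratum. No new data are needed, since prior-invitation status is already held for every girl. Stratifying removes the imbalance between samples; it does not remove selection within a sample, which is why the second change is needed as well.

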### Participant recruitment and randomisation

To be included in the study, participants will be selected randomly from a list of names of all girls aged 16-18 years, meeting the above inclusion criteria (See Figure 1). This list will be compiled by the Birmingham Primary Care Shared Services Agency (BPCSSA), which holds and controls all Birmingham patient data, from the names of all 16-18 year old girls eligible to be vaccinated against HPV. The list will be sorted according to whether girls have received a previous invitation to get vaccinated but have failed to attend their first session or have not previously received an invitation. BPCSSA will randomly select 500 participants to be included in the trial from each of these two sub-lists using the RAND() function in Excel. Selected individuals from both the samples will subsequently be separately randomised, via the aforementioned technique, to receive one of two invitations letters:

(a) A standard letter inviting them to attend their first vaccination session (Additional file 1) or

(b) A modified invitation letter, which will include the offer of vouchers worth £45 for receiving the three vaccinations (Additional file 1)

